Clarithromycin as adjunctive treatment to standard antibiotic therapy has been used by our group in two previous large-scale multi-center RCTs conducted in Greece after approval from the Greek regulatory authorities. The first RCT studied 200 patients with sepsis due to VAP and it was conducted between 2004 and 2005 ( [www.clinicaltrials.gov](http://www.clinicaltrials.gov) NCT00297674). Identified pathogens mainly included gram-negative bacteria i.e. *Acinetobacter baumanii* and *Pseudomonas aeruginosa* that do not belong to the usual antimicrobial spectrum of macrolides. Although 28-day mortality in both arms was similar, patients assigned to the clarithromycin arm experienced earlier weaning from mechanical ventilation and more rapid resolution of VAP, compared to the placebo arm. In the subgroup of patients with septic shock and multiple organ dysfunction syndrome (MODS), probability of sepsis-related death was significantly lower (OR 3.78 vs 19; *p* = 0.043). Serious adverse events (SAEs) occurred in 3 (3%) clarithromycin-treated patients, with no clear causative link with the study drug in 2 out of 3 cases^9^. Furthermore, hospitalization costs associated with clarithromycin use were significantly reduced (by 7000 euros/ patient that remained alive) compared to the placebo arm^10^.

The second multi-center RCT compared the efficacy of clarithromycin versus placebo added to standard antibiotic therapy in patients with gram-negative sepsis caused by acute pyelonephritis, intra-abdominal infections and primary gram-negative bacteremia; 600 patients were included between 2007 and 2011 ([www.clincialtrials.gov](http://www.clincialtrials.gov) NCT01223690). Overall mortality at 28 days in both arms did not differ, but probability of death due to septic shock and MODS was shown once more lower in the clarithromycin-treated group (OR 3.58 vs 6.21; p = 0.036). Interestingly, survival benefit from clarithromycin was even greater in those patients suffering from adult respiratory distress syndrome (ARDS). SAEs were described in 2 (0.7%) patients treated with clarithromycin, while its use was associated with saving of a median of 1000 euros/ hospitalized patient^11^. No QT space prolongation or any arrhythmia was observed in both aforementioned trials.

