***Cost-Effectiveness analysis***

The EuroCoL EQ-5D-3L^™^ questionnaire at 90 days (proxy and telephone version) data will be used to convert patient responses into Quality-Adjusted Life-Years (QALYs), to define patient-level perception of health-related quality of life on a 0,1 scale. Deceased patients will be counted as a 0 on that scale. Quality of life will be compared with the cost of hospitalization.

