**Secondary study endpoints**

To assess the effect of clarithromycin treatment compared to placebo treatment on the following:

- 28-day mortality in the subgroup of patients with septic shock
- All-cause 90-day mortality
- Early sepsis response, defined by an at least 25% decrease of day 1 SOFA score on day 3
- Sepsis resolution; this is defined by an at least 25% decrease of day 1 SOFA score on day 7
- New sepsis episode until day 28. A new sepsis episode is defined as a further increase of SOFA score by at least 2 points consequent to infection, in a patient who has experienced previous sepsis resolution (at least 25% decrease of day 1 SOFA score on day 7)
- Time until new sepsis episode. A new sepsis episode is noted in any patient who experiences any more than 25% decrease of day 1 SOFA score on day 7 and who has further increase of SOFA by at least 2 points, consequent to infection
- Biomarkers of sepsis-induced immunosuppression, through genome, metabolome, transcriptome, microbiome and cell population analysis
- The (primary) health economic outcome is cost per quality-adjusted life-year (QALY) gained for clarithromycin compared with placebo.

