**STATISTICAL ANALYSIS**

Qualitative endpoints will be analyzed by the Fisher’s exact test or continuity corrected Chi- square test, as appropriate. Logistic regression models will be used to evaluate variables associated with 28-day mortality. The effect on sepsis-induced immunosuppression will be a composite endpoint and it will result from the bioanalysis of gene expression, circulating cytokines and stimulated cytokines of patients. More precisely, bioanalysis of gene expression is anticipated to provide pathways modulated by treatment. These pathways will be validated by measurement of representative cytokines in cell supernatants. Comparisons of over-time changes will be done between the two groups of treatment. A p - value lower than 0.05 will be considered statistically significant, unless stated otherwise.

For the cost analysis, cost of each intervention will be counted and compared between groups, with non-parametric Mann-Whitney test, as previously described^10^. This analysis will be subject to robustness control to assess potential differences between different methods of cost calculation. Cost-effectiveness will be expressed as an incremental cost-to-effectiveness ratio (ICER) of clarithromycin compared with placebo, in a within-trial analysis (90 days). The ICER will be compared to a willingness-to-pay factor, which is either defined by the National Institute for Health and Care Excellence threshold or by per capita Gross Domestic Product. ^19, 20^

To evaluate the variation and significance of the ICER estimate, a bootstrapping method will be used.

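### The comparison of the ICER with a threshold has no rule for a zero or negative QALY difference, and bootstrapping the ratio does not supply one

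*Supplement*

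**What the plan says.** Protocol version 2, Secondary study endpoints, defines the economic outcome as a ratio: "The (primary) health economic outcome is cost per quality-adjusted life-year (QALY) gained for clarithromycin compared with placebo". The SAP lists the same outcome.

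The Statistical analysis section of the protocol sets out the method. Cost-effectiveness is expressed as an ICER over 90 days, and "The ICER will be compared to a willingness-to-pay factor". No amount is stated for that threshold, and its source is left open between two options: "which is either defined by the National Institute for Health and Care Excellence threshold or by per capita Gross Domestic Product". For uncertainty: "To evaluate the variation and significance of the ICER estimate, a bootstrapping method will be used".

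On how deaths enter the QALY, the Cost-Effectiveness analysis section says: "Deceased patients will be counted as a 0 on that scale".

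I found no rule in either document for a zero or negative QALY difference. Neither mentions dominance, the cost-effectiveness plane, net benefit or an acceptability curve. The SAP (General principles) moves the whole cost-effectiveness analysis to a separate report and adds no rule, so the protocol paragraph is the only specification.

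**The concern.** An ICER can be set against a threshold only when the new treatment gains QALYs. When it loses them, the ratio changes meaning, and the same number can describe the best and the worst result. At a QALY difference of zero it is undefined.

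A QALY difference near or below zero is a realistic outcome here. Deaths score 0, so an excess of deaths on clarithromycin pulls the difference down. The Introduction reports that overall 28-day mortality did not differ between arms in either earlier trial; the benefit came from subgroups.

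At stake is the health-economic conclusion. If the estimate falls on the wrong side of zero, the plan gives the analyst a number that cannot be read without a rule the plan does not contain.

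**Working it through.** **Inputs from the documents.** 55 patients per arm, and mortality of 55% on placebo and 30% on clarithromycin (Power calculation). Deaths scored 0 and a 90-day horizon. The documents state no cost, utility or threshold amount for this analysis. The only figure that can be reproduced is the sample size: a two-sided alpha of 0.10, power 0.8 and a continuity correction give 55 per arm, as stated.

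**Assumptions.** Threshold L of 20,000 or 30,000 per QALY, in the currency of the costs. Survivor utility with mean 0.6 and SD 0.25. Survival to day 90 equal to 1 minus the stated mortality. No missing data.

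**Step 1: the ratio loses the sign.** Let dC and dE be the cost and QALY differences (clarithromycin minus placebo), ICER = dC/dE, and net monetary benefit NMB = L x dE - dC.

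| dC (EUR) | dE | ICER | NMB, L = 20,000 | NMB, L = 30,000 |
|---|---|---|---|---|
| -5,000 | +0.05 | -100,000 | +6,000 | +6,500 |
| +5,000 | -0.05 | -100,000 | -6,000 | -6,500 |
| -1,000 | -0.02 | +50,000 | +600 | +400 |
| -300 | -0.02 | +15,000 | -100 | -300 |

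The first two rows are a dominant and a dominated result with the same ICER. In the last two rows health is lost and money saved. The larger saving gives an ICER above both thresholds although its NMB is positive, and the smaller saving gives one below both although its NMB is negative.

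**Step 2: the reversal is general.** Read "compared" in the ordinary way: favourable if ICER < L. For dE < 0, multiplying by dE turns the inequality round: dC/dE < L means dC > L x dE, that is, NMB < 0. For dE > 0 the two agree. So they disagree exactly when dE is negative, whatever the threshold or costs.

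**Step 3: how often is dE negative?** On the 0-1 scale (multiplying by 90/365 does not change a sign), an arm with survival s has mean 0.6s and variance s(0.6² + 0.25²) - (0.6s)². The standard error of dE is the square root of the sum of the two variances divided by 55.

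- No effect: 50%.
- Design effect, s = 0.70 against 0.45: dE = 0.150, SE = √((0.1194 + 0.1172)/55) = 0.0656, z = 2.29, so P(dE < 0) is about 1%. A simulation of 200,000 draws also gives about 1%.
- Half the design effect, s = 0.575 against 0.45: dE = 0.075, SE = √((0.1239 + 0.1172)/55) = 0.0662, z = 1.13, about 13%.
- Moderate harm, s = 0.40 against 0.50: dE = -0.060, SE = √((0.1114 + 0.1213)/55) = 0.0650, z = -0.92, about 82%.

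**Step 4: dominated results below the threshold.** Under no effect, if cost and QALY differences are independent, 25% of trials fall in each quadrant, so 25% are dominated. If survivors cost more than deaths (assumed means EUR 30,000 and 15,000, 45% mortality in both arms), the share is about 20%. All of these have a negative ICER, below any positive threshold.

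**Step 5: the bootstrap.** In a simulation of 400 null trials on the 0-1 scale, the 95% bootstrap interval for dE included zero in 94%. The resampled ICERs then come from both sides of zero. A value of -100,000 may be the best or the worst outcome, so percentiles of the ratio do not run from good to bad.

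**The case against.** **The decision rule is inferred.** The protocol says the ICER is compared with a threshold. It does not say that a value below it is accepted, nor that a negative value counts as favourable. A reader might infer that the plan commits the trial to passing a dominated drug. The documents do not support that. The phrase "cost per quality-adjusted life-year (QALY) gained for clarithromycin compared with placebo" presupposes a gain, and a competent health economist would probably check the quadrant unprompted. What stands is that nothing requires the check.

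**A reader might infer that the ratio gives too many favourable verdicts when the drug does nothing.** That does not follow. Any comparison of point estimates is favourable about half the time at the null, net benefit included. The ratio comparison gave 53-65% in one set of simulated assumptions and 40-46% in another (90-day scale), against about 50% for net benefit. The fault lies in which results look favourable.

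**A reader might infer that a harmful drug would almost surely pass.** That depends on the assumed cost. With mortality of 55% on clarithromycin against 30%, and survivors EUR 15,000 dearer than deaths, clarithromycin is 0.25 x 15,000 = EUR 3,750 cheaper. The ratio then falls below the threshold in 19-29% of trials (90-day scale) or 33-83% (0-1 scale). Near-certain passing needs a large added drug-arm cost. The only cost figures in the documents are savings, such as costs "significantly reduced (by 7000 euros/ patient that remained alive" in the first earlier trial.

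**The signs will be visible elsewhere.** Mortality at 28 and 90 days and costs by arm are reported, so a reader could detect a dominated result. That limits the harm, but does not make the ratio or its bootstrap interpretable. The plan also names no null value or interval type, so the remark on percentiles applies to the usual percentile interval.

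**Conclusion.** The point holds as a gap in specification joined to a poorly behaved summary. The sign loss and the reversal for a negative QALY difference are algebra and need no assumed figures, beyond the ordinary reading of the comparison. The frequencies rest on assumed utilities and costs: about half of trials disagree with net benefit under no effect, about 13% at half the design effect and about 1% at the full design effect. About 20% of null trials are dominated results below the threshold (25% if cost and QALY differences are independent).

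The importance is modest. The outcome is secondary and reported separately, and the gap hardly matters if the planned mortality benefit is real. It matters when the effect is small, absent or adverse. It should be mended because the remedy is nearly free.

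**What to change.** Amend the cost-effectiveness paragraph of the protocol's Statistical analysis section, or put the same text in the plan for the separate economic report:

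- Name one willingness-to-pay threshold, with its amount and currency, before unblinding, in place of the present choice between two sources.
- Base the conclusion and its uncertainty on incremental net monetary benefit: threshold x QALY difference - cost difference.
- Bootstrap patients within arm, keeping each patient's cost and QALY together. Report the interval for net benefit, the cost-effectiveness plane and the acceptability curve.
- Keep the ICER as a descriptive figure, quoted only when the cost and QALY differences are both positive. Otherwise state dominance or the quadrant in words.

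I do not propose that the interval for net benefit must exclude zero before a conclusion is drawn; that is a separate trade-off for the sponsor. The cost is a little more wording and analysis on bootstrap samples that are already planned, with no new data.

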**DURATION OF THE STUDY**

The duration of the study is estimated to two years after approval by the Greek and Belgian regulatory authorities.

**ADVERSE EVENTS**

Adverse events (AEs) and Serious Adverse Events (SAEs) will be collected from baseline until the last patient’s last evaluation. An adverse event is any undesirable medical occurrence in a subject receiving a pharmaceutical product and which does not necessarily have a causal link with this treatment. The adverse event may be a sign, a symptom, or an abnormal laboratory finding.

An adverse reaction is any undesirable and unintended reaction due to investigational medicine product administration (or intervention), related with any dose administrated. If an adverse event/ reaction meets any of the following criteria, it is considered as a *Serious Adverse Event/ Reaction* (SAE):

- Death
- Life-threatening situation The subject was at risk of death at the time of the adverse event/ experience. It does not refer to the hypothetical risk of death if the AE/ adverse reaction were more severe or were to progress.
- Hospitalization or prolongation of existing hospitalization
- Persistent or significant disability/ incapacity Any AE having an outcome that is associated with a substantial disruption of the ability to carry out normal life functions, including the ability to work. This is not intended to include transient interruption of daily activities.
- Congenital anomaly/ birth defects Any structural abnormality in subject’s offspring that occurs after intrauterine exposure to treatment.
- Important medical events/ experiences that may not result in death, be life-threatening, or require hospitalization, may be considered as SAE when, based upon appropriate medical judgment, they may jeopardize the subject and may require medical or surgical intervention to prevent one of the outcomes listed above, i.e. death, a life-threatening adverse event/experience, inpatient hospitalization or prolongation of existing hospitalization, a persistent or significant disability/ incapacity, or a congenital abnormality/ birth defect. Examples of such medical events/ experiences include allergic bronchospasm requiring intensive treatment in an emergency room or at home, blood dyscrasias or convulsions that do not result in inpatient hospitalization, or the development of drug dependency or drug abuse.
- Spontaneous and elective abortions experienced by study subject

*A non-serious adverse event* is one that does not meet the previous definition of a SAE. The severity of the non-serious adverse events will be graded using the following definitions:

- *Mild* - the adverse event/ reaction is transient and well tolerated by the patient
- *Moderate* – The adverse event/ reaction causes discomfort and affects the usual activities of the patient.
- *Severe* – The adverse event/ reaction affects the usual activities of the patient to an important degree and may cause disability or be life-threatening.

*Relationship with the drug*

The time relationship is established if the AE occurs during therapeutic treatment and until 5 half-lives after treatment discontinuation. The investigator will use the following definitions to assess the relationship of the adverse events with the study drug:

- Probably Related: The adverse event has a strong time relationship with the drug or relapses if re-induced, and another etiology is improbable or clearly less probable.
- Possibly Related: The adverse event has a strong time relationship to the drug and an alternative etiology is as probable or less probable.
- Probably not Related: The adverse event has a slight or no time relationship to the drug and/or there is a more probable alternative etiology.
- Unrelated: The adverse event is due to an underlying or concomitant disease or to another pharmaceutical product and is not related to the drug (no time relationship and a much more probable alternative etiology).

If an investigator’s opinion of possibly related, probably not related or not related to study drug is given, an alternative etiology must be provided by the investigator. Please note that a severe adverse event/ experience is not necessarily serious, as the term severe is a measure of intensity, while a serious adverse event is determined based on the aforementioned regulatory criteria.

Individual un-blinding thought to be necessary for the management of an adverse event will be documented in the subject CRF.

All Investigators are held to report every adverse event and evaluate the severity and possible causality with the study drug according to aforementioned criteria. All adverse events/ reactions are reported to Sponsor. The sponsor is responsible for the evaluation of all AEs. All Serious Adverse Events/ Serious Adverse Reactions must be reported to the Sponsor within 24 hours after having the information, by completion of the SAE form and fax to Hellenic Institute of Sepsis. Untoward events resulting from sepsis or infection (such as death or non-resolving infection) will not be recorded as AEs or SAEs, since they are study endpoints.

The Sponsor must evaluate whether an adverse event is expected or not. A SAE may qualify for expedited reporting to regulatory authorities if it is determined to be a suspected, unexpected serious adverse reaction (SUSAR- an adverse reaction, the nature or severity of which is not consistent with the applicable product information -e.g. investigator’s brochure for an unauthorised investigational product or summary of product characteristics for an authorised product). The Sponsor is responsible for submitting expedited safety reports to the appropriate regulatory authority and ethics committee for all confirmed SUSARs. In the case of a fatal or life-threatening SUSAR, the Sponsor will notify the regulatory authorities and the ethics committee as soon as possible but in no case later than 7 calendar days after the Sponsor’s initial receipt of the information. For a non-life-threatening SUSAR, the report will be submitted no later than 15 days after the Sponsor is made aware of the event.

The Sponsor has the obligation to submit annually a drug safety updated report (DSUR) according to global experience to the appropriate regulatory authorities. The electronic submission to Eudravigilance will be performed through the Organization ID: HISS.

The above pharmacovigilance procedures will be performed on behalf of the Sponsor (Hellenic Institute for the Study of Sepsis) by the Consultant Company «SUSTCHEM Engineering P.Braimiotis-P. Scarlatos LTD», [name], and the Qualified Person for Pharmacovigilance (QPPV) will be [name]. (contact details in Appendix I).

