- Evaluation of resolution of the infection and potential recurrence of infection according to the judgment of the attending physician
- Evaluation of potential adverse events

Visit 10 is on day 10. Procedures of this day include:

- Recording of SOFA score (see APPENDIX II); available blood cell count, biochemistry, coagulation times, urine output, blood gases, available radiological findings, clinically relevant microbiology and antimicrobial susceptibility testing, administered antimicrobials, other administered drugs and need for source infection control either by percutaneous interventions or by any operation.
- Survival status
- Evaluation of resolution of the infection and potential recurrence of infection according to the attending physician
- Sampling of 33 ml of venous blood; 9ml is collected into one pyrogen-free tube; and 24ml is collected into EDTA-coated tubes
- Evaluation of potential adverse events

Visits 11-28 are on days 11-28 respectively. They include

- Recording of SOFA score if available
- Administered antimicrobials, other administered drugs and need for source infection control either by percutaneous interventions or by any operation.
- Survival status
- Evaluation of resolution of the infection and potential infection recurrence according to the judgment of the attending physician
- Evaluation of potential adverse events

If the patient is discharged before day 28, a phone call will be performed on day 28 to assess survival status, need for new hospitalization or antibiotic therapy and potential adverse events. End-of-life decisions, if any, will be recorded.

Last visit: A phone call follow-up will be done on day 90 to assess survival status. If available, data concerning any new hospitalization, or antibiotic cure and potential adverse events will be collected during that phone call. Moreover, a self or proxy-assessment of health-related quality of life will be performed through the EQ-5D-3L^™^ questionnaire on the same visit (see APPENDIX IV) ^18^.

All information will be recorded on a specific paper Case Report Form (CRF).

The procedure to follow at each study visit is shown in APPENDIX V.

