| Resolution/ recurrence of infection** |  |  |  |  |  |  | x | x | x | x | x | x | x | x | x | x | x | x | x | x | x | x | x | x | x | x | x | x |  | |
| AE monitoring | x | x | x | x | x | x | x | x | x | x |  |  |  |  |  |  |  |  |  |  |  |  |  |  |  |  |  |  |  | |
| Microbiology** | x | x | x | x | x | x | x | x | x | x | x | x | x | x | x | x | x | x | x | x | x | x | x | x | x | x | x | x |  | |
| Pregnancy test*** | x |  |  |  |  |  |  |  |  |  |  |  |  |  |  |  |  |  |  |  |  |  |  |  |  |  |  |  |  | |
| PAX Gene | x |  |  |  | x |  |  |  |  |  |  |  |  |  |  |  |  |  |  |  |  |  |  |  |  |  |  |  |  | |
| Serum metabolomics | x |  |  |  | x |  |  |  |  | x |  |  |  |  |  |  |  |  |  |  |  |  |  |  |  |  |  |  |  | |
| PBMCs isolation | x |  |  |  | x |  |  |  |  | x |  |  |  |  |  |  |  |  |  |  |  |  |  |  |  |  |  |  |  | |
| Stool sample | x |  |  |  | x |  |  |  |  |  |  |  |  |  |  |  |  |  |  |  |  |  |  |  |  |  |  |  |  | |

- * SOFA score: if available according to usual clinical practice. On days where SOFA components are not available (e.g. no blood analysis programed by the physician or discharged patient), the last known value will be recorded.
- ** If available and justified by clinical context ***For female patients of reproductive age

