**Safety outcomes**

- Adverse events (AEs)
- Serious adverse events (SAEs)
- Suspected unexpected serious adverse reactions (SUSARs)

Patients are followed-up daily until day 28 or hospital discharge (whatever comes first). In case of earlier discharge, the primary outcome, is assessed by phone call at day 28. 90-day mortality and quality of life by the EuroQol**^®^** 5-dimension 3-level (EQ-5D-3L) questionnaire (1), in case of discharge, are also assessed by phone call with the patient or their caregiver. Safety outomes are captured daily until day 28 or discharge (whichever comes first) and as patient or provider-reported events until day 90. All other secondary outcomes are assessed until day 28 or discharge.

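### The Appendix V schedule stops AE monitoring at visit 10 although the text and SAP run it to day 28 and beyond, and an open-ended exclusion keeps sepsis-attributed events out of the AE/SAE record

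*Supplement*

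**What the plan says.** **Collection window.**
- Protocol version 2, Adverse events: AEs and SAEs "will be collected from baseline until the last patient’s last evaluation". The last visit is the day-90 telephone call.
- Protocol version 2, Study visits: "Visits 11-28 are on days 11-28 respectively. They include" an assessment for adverse events. For a patient discharged early, the day-28 call asks about survival and about "need for new hospitalization or antibiotic therapy and potential adverse events". The day-90 call also collects adverse events, where the information is available.
- SAP, Safety outcomes (the section listing the outcomes): "Safety outomes are captured daily until day 28 or discharge (whichever comes first"; after that, events reported by the patient or a provider count until day 90.
- Protocol version 2, Appendix V: the row reads "AE monitoring | x | x | x | x | x | x | x | x | x | x". The cells for visits 11 to 28 and for the last visit are empty, and no footnote explains this.

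**What is recorded.** In the Adverse events section of protocol version 2, "If an adverse event/ reaction meets any of the following criteria, it is considered as a" serious event, and death is the first criterion listed. Later, "All Investigators are held to report every adverse event" and to judge its severity and causality. The same paragraph ends: "Untoward events resulting from sepsis or infection (such as death or non-resolving infection) will not be recorded as AEs or SAEs". The reason given is that such events are endpoints of the study.

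**What is analysed.** The SAP's analysis section on safety compares the percentages of patients with an AE, an SAE or a SUSAR by Fisher's exact test. It mentions neither the window nor the exclusion.

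**The concern.** The safety comparison depends on which events reach the database, and the plan leaves two parts of that unsettled.

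First, the schedule is a table that site staff can be expected to work from. If a site stops looking for adverse events after visit 10, it can say that it followed the protocol, yet it will have collected less than the SAP assumes.

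Second, whether an event results from sepsis is a judgement, and no section says who makes it or by what criteria. In septic patients with several failing organs, that judgement can be hard to separate from a possible drug effect. An event placed under sepsis is not just spared expedited reporting. It is not recorded as an AE or SAE, so it is never graded on the protocol's causality scale. This weighs more here because QT prolongation and prior arrhythmia do not exclude a patient, serial ECGs are not required, and no interim analysis is planned.

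**Working it through.** There is no planned figure to reproduce. The check compares the sections and sizes the gap.

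**1. The window, side by side.**

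| Source | AE capture |
| --- | --- |
| Protocol v2, Adverse events | baseline to last evaluation |
| Protocol v2, Study visits | visits 1 to 28; day-28 call if discharged; day-90 call if available |
| SAP, Safety outcomes | daily to day 28 or discharge; reported events to day 90 |
| Protocol v2, Appendix V | visits 1 to 10 |

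Three of the four agree that capture goes past day 10; the table alone does not. The blanks are not a convention of the table, because its Survival row is marked at visits 2 to 28 and at the last visit. The AE row carries the same marks as the equivalent table in protocol version 1, although version 2 added AE questions at the day-28 and day-90 calls. That points to an omission carried over rather than a decision.

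**2. Size of the window gap.** Daily visits without an AE mark: 28 − 10 = 18, and 18/28 = 64%. This is the maximum, for a patient alive and in hospital to day 28 at a site that follows the table. It is smaller for anyone who dies or is discharged earlier, and zero at a site that follows the text. Dosing runs on days 1 to 4, so the marked visits cover treatment and 10 − 4 = 6 further days.

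**3. Scope of the exclusion against its reason.** The reason is that the events are endpoints. The clinical endpoints are all-cause mortality at 28 and 90 days (28-day mortality also in the septic-shock subgroup), SOFA-based response at days 3 and 7, and new sepsis episodes. The exclusion differs from that list in two ways:
- It takes in only sepsis-attributed deaths, while the mortality endpoint counts every death.
- It takes in any untoward event resulting from sepsis or infection, with death and non-resolving infection only as examples. A sepsis-attributed arrhythmia is no endpoint. Organ failure reaches the endpoints only through SOFA, which is recorded if available after day 10, with the last known value entered when components are missing.

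The causality scale already provides for these events. Its lowest grade covers underlying disease, and its possible grade covers an alternative cause that is equally probable.

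**4. Size of the exclusion for deaths.** The planning rates are 55% (placebo) and 30% (clarithromycin), with 55 patients per arm.
- Placebo: 55 × 0.55 = 30.25
- Clarithromycin: 55 × 0.30 = 16.5
- Total: 46.75, about 47 of 110

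The documents give no share attributed to sepsis, so the deaths left out of the SAE count lie between 0 and about 47.

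**The case against.** A general definition followed by an exception with a stated reason is not a contradiction. A reader might infer that the protocol contradicts itself on death, or that some 47 deaths vanish. The documents support neither. Deaths not due to sepsis remain SAEs, and every death is captured through the 28-day and 90-day all-cause endpoints and compared by arm in the ITT population.

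A reader might also infer that a fatal drug effect could never become a SUSAR. That presumes it has been misclassified: an event suspected to be a drug reaction falls outside the exclusion, and the protocol has a 7-day route for fatal SUSARs. Under the SAP only the study pharmacist is unblinded, so attribution is made blind, which limits differential filtering between arms.

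On the window, three texts agree and only a table row differs. Nothing shows that any site followed the row. Nor would it make the arms non-comparable across sites: randomisation is stratified by site, so a site's window applies to both arms.

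Most of this stands, and it narrows the point to under-collection and loss of causality data. It does not remove the mismatch in the table. It does not make the exclusion fit its stated reason, supply an attribution rule, or explain how the exclusion sits beside the duty to report every adverse event. Blinding does not restore events that were never recorded. The limit of five half-lives after treatment in the causality section restricts relatedness, not collection, and the SAP compares AE percentages without requiring relatedness.

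**Conclusion.** The point holds in two parts. The Appendix V row conflicts with the protocol text and the SAP, and must be aligned with them. The cost of leaving it is under-counted AEs and a less sensitive comparison, at most 18 of 28 daily visits per patient, and only where a site follows the table and the patient stays in hospital to day 28. It would be wrong to state this as 64% of the window lost.

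The exclusion of sepsis-attributed events is a deliberate exception, but it is wider than its reason and removes events from causality grading without an attribution rule. Between 0 and about 47 deaths could be absent from the SAE count, if the planning rates hold; the upper end assumes that every death is attributed to sepsis. The primary and other mortality analyses are not affected. This should be corrected, but it does not threaten the main result.

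**What to change.** 1. **Appendix V.** Extend the AE monitoring row to visits 11 to 28 and the last visit, so that it agrees with the Study visits text, the Adverse events section and the SAP.
2. **Protocol, Adverse events.** Reconcile the SAE definition, the duty to report every adverse event and the exclusion. Limit the exemption to events actually captured as endpoints, and keep a blinded causality assessment on record for deaths and other serious events. State who attributes an event to sepsis and how.
3. **SAP, safety analysis.** State the exclusion and the capture window. Present all-cause deaths by arm beside the AE/SAE table, and show SAEs with and without sepsis-attributed events where these were recorded.
4. **Patients already enrolled.** The SAP dates from the end of enrolment, before unmasking, database lock and the end of follow-up. Recover AEs for days 11 to 28 before unblinding, only where source records allow, and report the window actually captured. The CRF is not shown, so it cannot be assumed that its pages hold these data.

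Items 1 to 3 cost a protocol amendment, SAP wording and a causality entry for deaths already recorded as outcomes. They add no patient procedure. Item 4 takes real site effort and may be only partly feasible.
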